### Data Collection and Management

Clinical data, such as demographics, comorbidities, laboratory test results, procedures, medications, communications, office visits, and hospitalizations, as well as outcomes, such as 30-day readmission rates, for each patient are collected from the EHR. CRPM data, including raw physiological and operational data, clinical and operational notification data, and ePRO data, are collected from the vendor platform. All study information is being stored on NSUHS’s password-protected encrypted computers and password-protected servers.

Patients are given a unique study record number. The unique study record number is different from their medical record number. This unique record number is used to identify the patient on the vendor web platform. In addition to the study data, the study team collects patient name, medical record number, date of birth, and telephone number for the purpose of conducting the study and links this information to the unique study record number. This information and the key that links the unique study record number to the patient is stored on NSUHS’s secure server and only shared with the HHNs and the HF team involved in the study for patient care management. No personal health information is provided to the vendor or other study team members outside of NSUHS. All patient information is aggregated during study analysis, and no identifiers will be provided in the analysis. Upon study completion all study data will be destroyed, and verification will be provided to data governance.

During informed consent and enrollment, the study coordinator makes sure that patients are alone or in a room with family members who the patient agrees can participate in decision-making around the study. The door is closed, and the collection of any study-related information is paused when other staff or visitors enter the room. We allocate 1 hour for consent, and if required, we can extend the amount of time to make sure that the patient has all their questions answered and privacy maintained.

### Key Outcomes Measures and Statistical Analysis

We will conduct a mixed methods evaluation of the feasibility of the CRPM solution after the completion of all 3 phases of the study. Our primary end point will be to determine the feasibility of a 30-day CRPM solution and a cascading notification system. Feasibility will be assessed by evaluating the study completion rate and the study attrition rate between consent and end of the intervention and by evaluating provider and patient acceptability and satisfaction using the A-TAM [42]. We will use interviews to evaluate both patients’ and providers’ degree of technology acceptance; perceptions of, and satisfaction with, wearable biosensor patches; and satisfaction regarding escalation pathways. We will then carry out a directed content analysis of interview transcripts to identify specific themes informed by the A-TAM to help guide future implementations of continuous remote monitoring systems [46]. Specifically, researchers will conduct semistructured interviews with providers and patients. Different researchers will then analyze the interview transcripts and, using the A-TAM framework as a guide, they will identify significant phrases that represent each construct from the A-TAM. We will then develop a synopsis of the significant themes and their relationship to A-TAM constructs.

Preliminary efficacy will be determined by comparing the study group readmission rate with a retrospective cohort readmission rate. The retrospective cohort group will be created from patients with HF who meet the same inclusion and exclusion criteria and received usual care over the previous year. The patients in the control group will be matched based on demographics, discharge home with home health services, and clinical analytics prediction engine risk scores [43]. We will also evaluate whether continuous monitoring can improve care processes through an escalating feedback protocol by comparing clinical and outcome data in the CRPM group with those in a retrospective cohort control group. Comparative analysis will be performed using an interrupted time series design with a propensity-matched control group. The primary outcome measures and methods of evaluation are summarized in Table 1.

**Table 1 table1:** Primary aims and outcome measures.

Primary aim and measurement		Method of evaluation

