## Methods

### Study Design and Implementation

This is a prospective, mixed methods, nonrandomized, open-label feasibility study. Phase 1 (n=5) was the soft launch and has already been completed [39]. Phase 2 (n=15) is a calibration and testing period to evaluate, adjust, and optimize the alerting criteria, monitoring protocol, and workflows. Phase 3 (n=45) is the pilot period of the optimized study protocol. The study outcomes include feasibility and preliminary efficacy, as well as operational, process, and patient-related outcomes. Feasibility will be determined by evaluating provider and patient acceptability and satisfaction and by evaluating the study attrition and study completion rate. Provider and patient acceptability and satisfaction will be assessed through qualitative measures using the affective adaptation of the technology acceptance model (A-TAM) [42]. Preliminary efficacy will be determined by comparing the study group readmission rate with a retrospective cohort readmission rate.

The study will use the pinpointIQ (physIQ) solution to continuously remotely monitor patients with HF for 30 days after discharge. We will use rules-based and machine learning algorithms to analyze patients’ physiological data collected from the VitalPatch biosensor (VitalConnect) to identify patients potentially at risk of decompensation. A structured cascading escalation and management care pathway will be used to intervene on patients determined to be at risk for decompensation.

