### Participants

Participants will be recruited at NSUHS, which is a 9-hospital integrated health system in Chicago and surrounding suburbs in Illinois, United States. The intervention will be implemented at Evanston Hospital, a 354-bed hospital located in the Chicago suburbs, which has a cardiac care unit and an advanced HF cardiology consult service.

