### Recruitment

Eligible participants are recruited from patients hospitalized at NSUHS with an HF exacerbation. A daily enterprise data warehouse query is executed to identify patients hospitalized with an HF exacerbation who meet the eligibility determined by specific inclusion and exclusion criteria. Patients considered for participation have an HF diagnosis, have New York Heart Association functional class II to class IV symptoms, have received at least one dose of an intravenous (IV) diuretic during their hospitalization, have a plan for discharging with partnering home health services, speak English, and are in the top 50% of the patients stratified using NSUHS’s 30-day readmission risk–prediction model called the clinical analytics prediction engine [43]. Patients are not considered if they meet any of the exclusion criteria, which include having a CardioMEMS device; having an allergy to hydrocolloid gel adhesive; being pregnant; being on dialysis; or having a documented visual, cognitive, or physical impairment that would interfere with the ability to comply with the study procedures.

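### The readmission contrast sets consenting patients at one hospital against a previous-year cohort that is neither restricted to nor matched on that hospital and cannot be matched on willingness to take part

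*Protocol article*

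**What the plan says.** Under Key Outcomes Measures and Statistical Analysis, the article states: "Preliminary efficacy will be determined by comparing the study group readmission rate with a retrospective cohort readmission rate". The controls are "patients with HF who meet the same inclusion and exclusion criteria and received usual care over the previous year", and they are to be "matched based on demographics, discharge home with home health services, and clinical analytics prediction engine risk scores". The same section adds: "Comparative analysis will be performed using an interrupted time series design with a propensity-matched control group".

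The Participants section gives the recruitment frame as the whole system ("Participants will be recruited at NSUHS, which is a 9-hospital integrated health system") and then places the program at one site: "The intervention will be implemented at Evanston Hospital". It describes that site as having a cardiac care unit and an advanced heart failure consult service. The Recruitment criteria refer to the health system, and none names a hospital. The article describes the study as follows: "This is a prospective, mixed methods, nonrandomized, open-label feasibility study". Its Limitations section mentions the small sample and the restriction to home health patients. It does not mention the historical control or the selection of volunteers.

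**The concern.** If the text is followed as written, the control pool may come from all nine hospitals, in an earlier year, and include every eligible patient. The treated group is made up of patients at one hospital who agreed to wear a patch, change it repeatedly, carry a study phone and answer a daily survey. The two groups may therefore differ in site and in motivation as well as in exposure to the program.

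Preliminary efficacy is part of the stated objective, and Future Works says the study prepares for a larger efficacy trial. A readmission difference that partly reflects who was counted, and where, would feed into that decision, and the Limitations section would not warn the reader.

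**Working it through.** The article gives no target reduction, significance level or power calculation, so there is no planned figure to reproduce. The check has two parts.

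**1. What each planned device can remove**

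- *Same eligibility criteria.* These align diagnosis, symptom class, IV diuretic use, home health plan, language and the upper half of the risk model. They do not align hospital, because no criterion names one. They do not align consent, because controls were never asked.
- *Matching and propensity score.* The listed variables are demographics, home health discharge and risk score. Hospital is not listed. Willingness to take part is unrecorded for past patients, so no propensity model can include it.
- *Interrupted time series.* In simple form, the step at the interruption = program effect + change in site mix + change in volunteer mix + any abrupt calendar change. The fitted trend removes smooth drift only. If the earlier series holds all eligible patients and the later one only consenting patients at one hospital, the site and volunteer terms appear as a level change, exactly where a program effect would appear. The later series is also thin: 5 + 15 + 45 = 65 patients over three phases, with survey, workflow and the machine-learning alert altered after phase 1.

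**2. How large a volunteer effect could be**

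Inputs: background readmission rate p of 17% to 28.2% (Background section; published Medicare figures, not the trial's own control rate). Assumption, not from the documents: after matching, volunteers' risk is still 10%, 20% or 30% below that of all eligible patients, so the risk ratio RR is 0.9, 0.8 or 0.7. Spurious difference with no program effect = p × (1 − RR), in percentage points:

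| p | RR 0.9 | RR 0.8 | RR 0.7 |
|---|---|---|---|
| 17% | 1.7 | 3.4 | 5.1 |
| 28.2% | 2.8 | 5.6 | 8.5 |

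For scale, the 95% half-width of one rate with 65 patients is 1.96 × √(p(1 − p)/65). This is 1.96 × √(0.17 × 0.83/65) = 9.1 points at 17%, and 1.96 × √(0.282 × 0.718/65) = 10.9 points at 28.2%. Chance error is therefore at least as large as the assumed bias. Chance error shrinks with more patients; the bias does not.

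**3. Would non-enrolled patients be a better main comparator?**

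The daily query ("A daily enterprise data warehouse query is executed to identify patients hospitalized with an HF exacerbation") could identify same-month eligible patients who did not enroll. Illustration, all assumed: the average risk is 25%, half of eligible patients consent, and volunteers have 0.8 of the average risk.

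- Volunteers: 0.8 × 25% = 20%.
- Decliners: (25% − 0.5 × 20%)/0.5 = 30%.
- Gap against all eligible patients: 25 − 20 = 5 points.
- Gap against decliners only: 30 − 20 = 10 points.

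The concurrent group helps with calendar time, and with site if taken from the same hospital. To the extent that it consists of decliners, it can double the volunteer bias.

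**The case against.** The case for leaving the plan alone is substantial. The primary end point is feasibility. Efficacy is labelled preliminary, significance testing is disclaimed, and effectiveness is deferred to a later trial. The nonrandomized, open-label design is stated openly. Controls are matched on a readmission risk score and on home health discharge, a propensity match is named, and the time series is meant for secular trend. A condensed article may also leave a site restriction to the full protocol.

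Much of this stands, and it limits what can be claimed. Four stronger readings are tempting but unsupported:

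- *The bias is as large as the reduction sought.* No target reduction is stated, so there is nothing to compare it with.
- *Calendar time is wholly confounded with treatment.* The named time series partly addresses it.
- *The same eligibility criteria cannot be applied to past patients.* Consent and acceptance of the device are not listed criteria, and the impairment exclusion refers to documented impairment, which can be sought in the chart. Some judgment remains about interference with study procedures, but volunteer selection is a separate matter.
- *The bias favours the program.* A hospital with an advanced heart failure service may treat sicker patients, which would work against it.

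What the objection does not answer is hospital and willingness to take part. The article does list its matching variables, and hospital is not among them. None of the named methods removes a change in site or volunteer mix at the interruption.

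**Conclusion.** The point holds in a limited form. As written, the readmission contrast mixes the program's effect with differences in site and volunteer selection that the planned matching and time series do not remove. The direction and size of the bias are unknown. The 1.7 to 8.5 point range covers volunteer selection only. It rests on an assumed 10-30% lower risk that persists after matching on risk score, and on the article's quoted 17%-28.2% rates. It shows what is possible, not what will occur. The site effect cannot be sized from the document.

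The conclusion takes treated patients' index stays to be at the intervention hospital, as the Participants section indicates, and assumes that no fuller document restricts the controls by site. It does not touch the feasibility end point. It is worth correcting because the site part costs little to fix and a larger sample would not cure it.

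**What to change.** 1. Restrict controls to index discharges from the intervention hospital, or match exactly on hospital. The home health requirement is already in the plan. Cost: a smaller control pool.
2. Keep the previous-year cohort as the main comparator. Add, as a secondary sensitivity comparison, eligible non-enrolled patients discharged in the same months, identified through the existing query. Separate decliners from those not approached where this is recorded. State that decliners are themselves a selected group, which can exaggerate benefit, and that spill-over of the new workflow can bias toward no effect. Cost: one further record extraction. The article does not say that query results are kept, and it plans to destroy study data on completion, so this should be settled before then.
3. Report the fraction of eligible patients who consented, and name the historical control and volunteer selection in the Limitations section as limits on the readmission conclusion. Cost: a screening count and a few sentences.

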**Methods:**

This study is a feasibility study and uses a wearable biosensor to continuously remotely monitor patients with HF for 30 days after discharge. Eligible patients admitted with an HF exacerbation at NorthShore University HealthSystem are being recruited, and the wearable biosensor is placed before discharge. The biosensor collects physiological ambulatory data, which are analyzed for signs of patient deterioration. Participants are also completing a daily survey through a dedicated study smartphone. If prespecified criteria from the physiological data and survey results are met, a notification is triggered, and a predetermined electronic health record–based pathway of telephonic management is completed. In phase 1, which has already been completed, 5 patients were enrolled and monitored for 30 days after discharge. The results of phase 1 were analyzed, and modifications to the program were made to optimize it. After analysis of the phase 1 results, 15 patients are being enrolled for phase 2, which is a calibration and testing period to enable further adjustments to be made. After phase 2, we will enroll 45 patients for phase 3. The combined results of phases 1, 2, and 3 will be analyzed to determine the feasibility of a CRPM program in patients with HF. Semistructured interviews are being conducted with key stakeholders, including patients, and these results will be analyzed using the affective adaptation of the technology acceptance model.

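### The interrupted time series named for the comparative analysis does not fit the data described and conflicts with the plain rate comparison stated in the same section

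*Protocol article*

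**What the plan says.** The efficacy comparison is stated under Study Design and Implementation and repeated under Key Outcomes Measures and Statistical Analysis: "Preliminary efficacy will be determined by comparing the study group readmission rate with a retrospective cohort readmission rate". The latter section describes the controls as heart failure patients who "meet the same inclusion and exclusion criteria and received usual care over the previous year", matched on demographics, discharge with home health services and predicted readmission risk.

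The section next adds a comparison of care processes that uses clinical and outcome data from the same two groups. It then names a method: "Comparative analysis will be performed using an interrupted time series design with a propensity-matched control group". No other comparative method is named.

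The study group is built up in three steps. The first is over: "Phase 1 (n=5) was the soft launch and has already been completed". The second leaves the intervention open to change: "Phase 2 (n=15) is a calibration and testing period to evaluate, adjust, and optimize the alerting criteria, monitoring protocol, and workflows". The third takes in most of the patients once that tuning is done: "Phase 3 (n=45) is the pilot period of the optimized study protocol". The aim is to "continuously remotely monitor patients with HF for 30 days after discharge", so each patient supplies one 30-day readmission outcome. The abstract pools the phases for feasibility: "The combined results of phases 1, 2, and 3 will be analyzed to determine the feasibility of a CRPM program in patients with HF".

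**The concern.** A controlled interrupted time series compares the change in an intervention series with the change in a control series over the same dates. That needs control observations on both sides of the interruption and intervention-group observations before it. The article describes neither: the matched controls supply the period before and the enrollees supply the period after.

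The start of monitoring is not one clean interruption either. The account of the phase 1 results reports a more sensitive deterioration alert, a replaced symptom survey and a redesigned workflow. Phase 2 is set aside for further adjustment.

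Two things are at stake. The plan leaves two different analyses for one outcome, so the choice could be made after the results are seen. And if the time series is the one used, its level change could be reported as the effect of monitoring when it also carries the change of population and of calendar period, with much less precision than the simpler comparison offers.

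**Working it through.** The article gives no sample-size or power figure, so there is none to reproduce.

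**Inputs from the article**
- Study group: 5 + 15 + 45 = 65 patients, one 30-day outcome each (Study Design and Implementation).
- Controls: matched usual-care patients from the previous year (Key Outcomes Measures and Statistical Analysis).
- Background readmission rate: 17% to 28.2% (Introduction, Background).

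**Assumptions (not in the article)**
- Monthly points, with 12 months before and 6 to 24 months after.
- Matching 1:1 or 3:1.
- A central rate of 25%, independent outcomes and no autocorrelation.

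**Step 1: can the controlled model be identified?** The usual model has eight terms: intercept, time, post, post×time, group, group×time, group×post and group×post×time. Here group = 1 exactly when post = 1. So group and group×post both equal post, and group×time and group×post×time both equal post×time. Only four distinct columns remain: the design matrix has rank 4 of 8. The matched controls cannot separate monitoring from period, and a larger sample would not change that.

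**Step 2: precision of the direct comparison.** The 95% half-width is 1.96 × √[p(1−p)(1/n₁ + 1/n₀)].
- p = 0.25, 65 vs 65: 1.96 × √(0.1875/65 + 0.1875/65) = 0.149, about ±15 points.
- p = 0.25, 65 vs 195: 1.96 × √(0.1875/65 + 0.1875/195) = 0.122, about ±12 points.

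**Step 3: precision of an uncontrolled segmented model.** With separate trends before and after, the level change is the gap between two fitted lines at the interruption, which lies at the end of each segment. For M equally spaced, equally sized monthly points, the variance of a fitted line at the segment end, relative to that of the segment mean, is

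1 + (M/2)² / [(M² − 1)/12] = 1 + 3M²/(M² − 1).

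For M = 12 this is 1 + 3 × 144/143 = 4.02. It is close to 4 for any plausible M, so the standard error is about √4 = 2 times that of the direct contrast, almost regardless of the number of months. At p = 0.25 and 1:1 matching that gives 2 × 14.9 = 29.8, about ±30 points. A simulation of 3,000 runs gave 0.30, 0.31 and 0.31 for 12, 18 and 24 post-months, and 0.24 with 195 controls.

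**Step 4: across the article's background rates** (95% half-widths in percentage points)

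| Rate | Matching | Direct | Segmented level change |
|---|---|---|---|
| 17% | 1:1 | 12.9 | about 26 |
| 17% | 3:1 | 10.5 | about 21 |
| 28.2% | 1:1 | 15.5 | about 31 |
| 28.2% | 3:1 | 12.6 | about 25 |

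**Step 5: how thin the series would be.** Over 12 post-months there are 65/12 = 5.4 patients a month and 0.9 to 1.5 expected readmissions. The chance of a month with none is (1 − p)^5.4, or 36% at the lower rate and 17% at the higher. Over 24 months there are 2.7 patients and 0.5 to 0.8 readmissions a month, with a 60% to 41% chance of none.

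The two quantities are not the same estimand. The level change refers to the moment of interruption; the risk difference averages over the whole period. The doubled standard error is the price of fitting separate trends.

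**The case against.** Several parts of the case for the plan stand.

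- **The plain comparison is already there.** A reader might infer that the readmission effect would come from the time series model. The article does not support that: it defines preliminary efficacy, twice, as a comparison of two rates. The time series sentence directly follows the care-process comparison and may have been meant for it. But its wording is not restricted to care processes, that comparison also covers outcome data, and the design problem is the same there.
- **Different people before and after are not the problem.** A reader might infer that an interrupted time series fails because each patient gives one outcome and the two periods contain different patients. Successive monthly discharges are an accepted series. The valid objection is narrower: consenting enrollees replace usual-care patients exactly at the interruption, and no concurrent control series is described.
- **The replacement is confounded too.** A risk difference against previous-year controls carries the same change of population and period. It gains precision and clarity, not identification.
- **The phase point has limits.** The Discussion says calibration ends in a fixed state before the pilot, so 45 of the 65 patients should receive a settled intervention. The abstract pools the phases expressly for feasibility, not for efficacy.
- **Low power is admitted.** The article says it cannot determine statistical significance, and it reserves efficacy for a later trial. Imprecision as such is therefore no error. Nor is the 17% to 28.2% span a target effect: it is 11.2 points wide, and most of the direct half-widths exceed it as well.
- **A fuller plan might define a wider series**, such as all heart failure discharges by month. That is possible, and leaving out the time unit is normal in an article. But the article names a method and describes data, and the two do not match.

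**Conclusion.** The concern holds at moderate severity. Key Outcomes Measures and Statistical Analysis contains two statements that need reconciling, and the second names a design that the described data cannot identify.

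Non-identification rests on one reading: that the retrospective controls all precede the study. If some overlapped with enrolment, a concurrent comparison would become possible. The study group would still have no series before the interruption, so the difference in change would remain unidentified.

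The doubling of the standard error depends little on the assumed number of months. The absolute figures, about ±30 against ±15 points, depend on the 25% rate, 1:1 matching and monthly points. Over the article's background rates and both matching ratios, the range is about ±21 to ±31 against ±10.5 to ±15.5.

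A reader might infer that the study's efficacy result is invalid or that the plan must not proceed. The documents do not support that. Preliminary efficacy belongs to the stated aim, but the primary end point is feasibility, the article disclaims power, and no decision rule rests on this estimate.

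**What to change.** Replace the interrupted time series sentence with the comparison already stated, for example:

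> Thirty-day readmission will be compared between study patients and the propensity-matched previous-year cohort as a risk difference with a 95% confidence interval that accounts for the matching. The result is exploratory.

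Add to the Limitations that controls are historical, so selection of enrollees and calendar time cannot be separated from the effect of monitoring. The replacement does not remove that confounding.

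If a time series is truly wanted, for readmission or for care processes, define a real one: the population that forms the series, the time unit, the number of points before and after, and a control series that runs through both periods.

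The first option costs one sentence and one limitation, needs no new data and reduces the modelling work. The second would need data beyond the two groups the article describes.
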